## Methods/design

### Justification of the study

Currently, there are no specific pharmacological therapies for COVID-19. There has been great interest in the role of corticosteroids to attenuate the pulmonary and systemic damage in patients with the acute respiratory distress syndrome (ARDS) because of their potent anti-inflammatory and antifibrotic properties [5]. Corticosteroids have been off-patent for greater than 20 years; they are cheap and globally equitable. Dexamethasone has potent anti-inflammatory effects and weak mineralocorticoid effects compared with other corticosteroids [11]. It is 20 to 30 times more potent than the naturally occurring hormone, cortisol, and four to five times more potent than prednisone [5]. In addition, dexamethasone has a long-lasting effect, allowing for a once-a-day regimen [11].

We justify the need of this study based on the positive results of a recent clinical trial, showing that dexamethasone for 10 days was able to reduce the duration of MV (between-group difference 5 days, 95% CI 2–8 days) and 60-day hospital mortality (between-group difference 15%, 95% CI 5–26%) in patients with ARDS from multiple causes [8], and on preliminary retrospective data demonstrating a decrease in mortality [4]. Our goal in this study is to examine the effects of dexamethasone on mortality and on ventilator-free days (VFDs) in patients with moderate-to-severe ARDS due to confirmed COVID-19 who still meet ARDS criteria at 12 h after ARDS diagnosis despite routine intensive management.

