### Outcome measures

The primary outcome is all-cause mortality at 60 days after randomization. Site investigators will be reporting patient status at 60 days, irrespective of whether the patient continued hospitalized in the same hospital, in another type of health care facility, or discharged home. If patients are discharged alive from hospital before day 60, the information on clinical status at 60 days will be obtained from the electronic clinical record. The Public Health Care System in Spain provides information about the clinical status of any patient through the electronic clinical record system that exists in any public hospital, city, province, or region. In the few cases in which no information could be not obtained from the electronic clinical record (e.g., the patient is not in contact with the outpatient clinic or home care professionals), the local investigator will contact the patient or relatives by phone to ensure the status of the patient at day 60 after randomization. In addition, lead investigators in each site will confirm the recorded 60-day mortality at the time of data analysis.

The secondary outcome is the number of VFDs at 28 days, defined as the number of days alive and free of MV from the day of randomization (day 1) to day 28 after enrollment, on which a patient breathe without assistance. For a day to be considered a ventilator-free day, the patient must breathe without assistance for the full 24 h, i.e., for every breath during that day. The following considerations will be taken into account when calculating the number of VFDs: (i) successful liberation from MV should last more than 48 h without reintubation in patients who survive 28 days after randomization; (ii) extubation only count from the last successful extubation within a 28-day survivor; and (iii) VFDs are awarded zero days if the patient is ventilated for 28 days or more, or die before 28 days (irrespective of intubation status) [20]. Other clinical outcomes include mortality in the ICU, mortality at day 28, duration of MV, length of stay in the hospital for survivors, and the time (in days) from treatment initiation to death. Virologic measures will include the proportions with viral RNA detection over time. Safety outcomes in both groups will include adverse events that occurred during treatment (hyperglycemia, new infections), serious adverse events, and premature discontinuation of treatment.

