### Sample size calculations

The trial was designed to be initiated in rapid response to the COVID-19 public health emergency. We estimated the sample size on the assumption that treatment with dexamethasone could reduce all-cause 60-day mortality by 20%. Our baseline reference was 50–55% based on recent observational studies from China [4]. Depending on the estimated 60-day mortality, we studied various group-size scenarios with cohorts of 93 to 100 patients in each arm to detect a 20% difference with a power of 80%, at a two-sided significance level of alpha = 0.05. The R function power.prop.test was used to estimate the sample size requirement which is based on a *z* test. A population size of 192 patients (96 in each arm) will provide 80% power to detect a 20% absolute reduction, from 55% on the control group to 35% in the experimental group. To account for up to 5% potential losses to follow-up, we will randomize 200 patients. We will only analyze patients that are enrolled and randomized to receive treatment. There will not be a formal interim analysis. However, after recruitment of 70% of the patients, an independent statistician will perform a conditional power analysis. If the conditional power at that time is ≥ 70% but < 80%, the external Data and Safety Monitoring Board (DSMB) can recommend an increase in sample size to achieve 80% power. The conditional power analysis will be performed at the Applied Health Research Center, Li Ka Shing Knowledge Institute of St. Michael’s Hospital, Toronto, Canada. Since the conditional power analysis will not be used to stop the trial early due to a treatment difference, no adjustment to alpha is required. The DSMB could decide to stop the trial at any point for safety reasons. Also, in a context of a pandemic, it is plausible to discontinue the trial if no new patients are enrolled during a prolonged period of time. The decisions of the DSMB will be communicated to the principal investigators in a letter (sent by email). If the DSMB reaches a decision that the trial must be terminated early for safety reasons, they will email and call either one of the PIs within 24 h of making this decision.

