Other continuous outcome variables will be compared with the Student’s *t* test. The treatment effect will be expressed as mean differences with 95% confidence intervals. For variables where there are major concerns about the underlying assumptions for the *t* test, the Mann-Whitney *U* rank test will also be used for a sensitivity analysis. Other categorical outcome variables will be compared using a chi-square test or Fisher’s exact test if expected counts are < 5. The treatment effect will be expressed as a risk difference with 95% confidence interval as well as the risk ratio. The time to hospital discharge will be summarized with cumulative incidence curves, treating death as a competing risk and compared using a cause-specific Cox model, and the treatment effect will be expressed as a hazard ratio with 95% confidence interval. Two-sided testing will be used for all inferential comparisons. A *p* value of less than 0.05 will be considered to indicate statistical significance for the primary outcome. Given the controversies around significance testing, *p* values will always be accompanied by point estimates of treatment effect and 95% confidence intervals. Analyses will be done by an independent statistician who will be unaware of group assignment.

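### Minor, nearly free improvement: use Welch's t test for hospital stay in survivors, where the planned mortality implies about 45 v 65 patients and a pooled-variance CI is miscalibrated if the SDs also differ

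*Protocol article*

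**What the plan says.** The Statistical analysis section fixes one method for continuous outcomes other than ventilator-free days (VFDs): "Other continuous outcome variables will be compared with the Student’s" *t* test. It then says: "The treatment effect will be expressed as mean differences with 95% confidence intervals". Where the assumptions of the *t* test are in serious doubt, a Mann-Whitney "rank test will also be used for a sensitivity analysis". An unequal-variance version is not mentioned.

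Outcome measures lists, among the other clinical outcomes, "length of stay in the hospital for survivors". It is the only continuous outcome there that is expressly limited to survivors. Duration of mechanical ventilation carries no such limit.

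Sample size calculations assumes that mortality falls "from 55% on the control group to 35% in the experimental group", with 96 patients per arm needed and 200 randomised. Randomization and masking sets a 1:1 ratio.

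**The concern.** Student's test estimates one common variance. With equal group sizes this is harmless even if the spreads differ. With unequal sizes it is not: if the smaller group has the larger SD, the pooled standard error is too small and the CI too narrow. If the larger group has the larger SD, the CI is too wide.

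Randomisation at 1:1 normally protects against this, but restricting an outcome to survivors removes that protection when mortality differs between arms, which is what the trial is designed to show. The interval matters because the section says that *p* values will always be reported with estimates and 95% CIs. The Mann-Whitney test does not repair the interval, because a rank test gives no corrected CI for a difference in means.

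**Working it through.** **Inputs from the protocol article.** Mortality 55% v 35%, two-sided alpha 0.05, power 80%, 96 per arm needed, 200 randomised (Sample size calculations); 1:1 allocation (Randomization and masking). **Assumed:** the SD ratio r = SD(control)/SD(dexamethasone), varied because no SD is given, and 60-day survival as the measure of who counts as a survivor.

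**1. The plan's own figure.** n per arm = [1.960·√(2·0.45·0.55) + 0.842·√(0.55·0.45 + 0.35·0.65)]² / 0.20² = (1.379 + 0.580)² / 0.04 ≈ 95.9, so 96. The stated sample size is reproduced.

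**2. Expected survivors.** 100 × (1 − 0.55) = 45 controls and 100 × (1 − 0.35) = 65 on dexamethasone. With 96 per arm the figures are about 43 and 62.

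**3. Why pooling goes wrong.** Set the dexamethasone SD to 1 and the control SD to r.
- Variance used by Student: [(44r² + 64)/108] × (1/45 + 1/65)
- True variance of the mean difference: r²/45 + 1/65

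At r = 1.5 these are 1.509 × 0.03761 = 0.0568 and 0.0500 + 0.0154 = 0.0654. The standard error used is √(0.0568/0.0654) ≈ 0.93 of the true one. At r = 1 the two agree.

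**4. Coverage of the nominal 95% CI at 45 v 65.** Simulated with 200,000 normal data sets per setting, and 100,000 skewed (lognormal) ones.

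| r | Student, normal | Welch, normal | Student/Welch width, normal | Student, skewed | Welch, skewed |
|---|---|---|---|---|---|
| 0.67 | 96.5% | 95.1% | 1.07 | 96.2% | 95.2% |
| 1.0 | 94.9% | 94.9% | 1.00 | 95.3% | 95.3% |
| 1.25 | 94.0% | 95.0% | 0.96 | 94.2% | 94.7% |
| 1.5 | 93.3% | 95.0% | 0.93 | 93.0% | 94.3% |
| 2.0 | 92.0% | 95.0% | 0.89 | 91.6% | 93.8% |

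For 43 v 62 and for 50 v 70 (mortality 50% v 30%), normal-data coverage differs from these values by less than half a percentage point.

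**5. Equal groups.** At n per arm the pooled variance term is [(s₁² + s₂²)/2] × (2/n) = (s₁² + s₂²)/n, the same as Welch's. Simulation at 100 v 100 gives Student coverage between 94.9% and 95.1% for every r from 0.5 to 2.

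**6. Cost of Welch when the SDs are equal.** At 45 v 65, for a difference set to give about 80% power, simulated power is 79.26% for Student and 79.14% for Welch. The Welch interval is about 0.15% wider.

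**The case against.** The strongest reply is that nothing here is contradictory. The article never says pooled or equal-variance, and an analysis plan that is not shown could specify the unequal-variance form. That is possible, but Student's *t* test is a named method with an ordinary meaning. The point is that a better-calibrated method could replace it, not that a detail is missing.

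The other objections limit the point, and they stand.

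- **Unequal SDs are also required.** A reader might infer that the trial's own assumptions make the interval too narrow. They fix only the group sizes; at r = 1 there is no loss.
- **The direction is open.** Justification of the study cites an earlier trial in ARDS of multiple causes in which dexamethasone could "reduce the duration of MV (between-group difference 5 days, 95% CI 2–8 days". If spread shrinks with the mean, controls would have the larger SD. But that result concerns ventilation, not hospital stay, and the survivors on dexamethasone could equally be the more variable group.
- **The likely size is small.** For illustration, take an assumed mean of 25 days, a fall of 5 days and a constant coefficient of variation: r = 25/20 = 1.25, about one point of coverage. Even a fall of 8 days gives only 25/17 ≈ 1.47.
- **Scope.** A reader might extend this to all continuous outcomes. Only hospital stay is explicitly survivor-only, and outcomes in all randomised patients keep 95% coverage.
- **Another analysis exists.** Time to hospital discharge is also analysed with death as a competing risk and a cause-specific Cox model. This lessens reliance on the *t* interval but does not correct it.

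**Conclusion.** The point holds as a minor improvement limited to hospital stay in survivors. If mortality is near 55% v 35% and the SDs differ, the pooled 95% CI for the mean difference covers about 94% to 92% for SD ratios of 1.25 to 2, and about 96.5% at 0.67. These ratios are assumptions, and the document does not say which applies.

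No main conclusion depends on it. The primary outcome uses a chi-squared test, VFDs use Mann-Whitney with a bootstrap CI, and the secondary outcomes are declared exploratory. Nor would it be right to infer that Welch removes the problem entirely at no cost: with skewed data its coverage is still 93.8% at a ratio of 2, and it has a very small cost in power. Conditioning on survival is a separate matter that the choice of variance estimator does not address.

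**What to change.** In Statistical analysis, name Welch's unequal-variance *t* test in place of Student's, at least for outcomes limited to survivors, and take the 95% CI of the mean difference from the same Welch statistic. Keep Mann-Whitney as the sensitivity analysis. The change is one phrase, needs no extra data, and leaves the sample size and the primary analysis as they are.

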### Trial organization

The steering committee is composed of the study principal investigators who contributed to its design and approved the final protocol (Appendix 2). The trial will be monitored by a DSMB. The DSMB can recommend to stop the trial because of safety concerns or recommend increasing the sample size to achieve 80% power based on a conditional power analysis. The DSMB will be composed of three external, independent experts in critical care medicine, mechanical ventilation, and ARDS, and a statistician (Appendix 2).

The study coordinator (JV) is responsible for promoting patient enrollment and complete follow-up, including a list of any outcome data to be collected from participants who discontinue or deviate from intervention protocols. The trial management team comprises the chief investigators, a project manager, a statistician, a clinical epidemiologist, and an investigator expert in clinical trials. The responsibilities of this team are as follows:
(i)Planning and conducting the study: designing the protocol, designing the randomization process, case report forms, and managing and controlling the data quality(ii)Assisting centers with administrative submission process of completed CRF, providing randomization, taking actions to increase patient enrollment, auditing, and sending study materials to the research centers(iii)Regular communication with enrolling centers for solving question related to screening and enrollment(iv)Providing update of published literature related to COVID-19 ARDS(v)Monthly monitoring of enrolled patients by each center(vi)Monitoring patient’s follow-up(vii) Producing a by-monthly study newsletter (DEXA-COVID19-news)(viii) Programing an online research-in-progress meeting when half of planned sample size patients are enrolled(ix)Statistical analysis, research reporting, and helping in writing the final manuscript

### Reporting adverse events

According to Spanish legislation, adverse events should be reported to the Trial Coordinator and to the referral Ethics Committee for review. All adverse events occurring during the study observed by the investigator will be recorded on the data forms. An adverse event is defined as any untoward medical occurrences in a patient during the trial that are not considered related to the clinical state of the patient. Serious adverse events related to the protocol will be sent to the DSMB within 24 h after being received by the trial coordinator. Expected adverse events or complications related to the protocol would include occurrence of hyperglycemia (blood glucose > 180 mg/dL) and new infections (e.g., pneumonia or sepsis) after randomization. All unexpected, and related or possibly related, adverse events will be reported to the institutional review board. Adverse events considered related to the trial, as judged by the investigators, will be followed until resolution or until the event is considered stable. Related adverse events that result in a participant’s withdrawal from the study or are present at the end of the study will be followed up until a satisfactory resolution occurs. The investigator would seek information on adverse events by specific questioning and examination.

## Discussion

This is a randomized controlled trial designed to evaluate the efficacy of dexamethasone in patients with established ARDS caused by SARS-CoV-2 and managed with a lung-protective ventilatory strategy, which includes the use of low tidal volume, application of moderate to high levels of PEEP, and limitation of the plateau pressures below 30 cmH_2_O.

Corticosteroids have been the most widely used medications for ARDS since the first clinical description of the syndrome [21]. However, the efficacy of corticosteroids in viral ARDS remains controversial [6, 7]. For a virus to survive and replicate in an organism, it must employ strategies to evade and misdirect the host’s immune response. There is compelling evidence that the primary immune-evasive strategy utilized by the coronavirus is to inhibit its host’s corticosteroid stress response [22]. This is accomplished by viral expression of amino acid sequences that are molecular mimics of the host’s adrenocorticotropic hormone (ACTH). When the host produces antibodies against these viral antigens, the antibodies bind to the host’s own ACTH, which limits the host’s stress response by interfering with ACTH’s ability to stimulate the secretion of corticosteroids. Influenza and coronavirus-infected patients do not have increased cortisol levels [23]. Influenza and coronavirus are cytokine dysregulators [24, 25]. The virus induces the release of inflammatory cytokines, which disrupts the immune response and can lead to multisystem organ dysfunction, including ARDS. Treatment with corticosteroids can relieve the patient’s symptoms of adrenocortical insufficiency and increase corticosteroid levels. Corticosteroids appeared to improve the clinical condition of patients with severe acute respiratory syndrome (SARS), as reported in several studies [26, 27].

In a recent commentary on the use of corticosteroids in severe viral epidemics, the authors stated that there are “conclusive data” to expect that patients with COVID-19 ARDS will not benefit from corticosteroids [6]. This interpretation is without full evidence-based support [28]. First, their “conclusive” statement rested on only four small studies without including results from another 25 publications [28]. Second, they ignored the positive findings of two large studies showing a reduction in mortality in 401 patients with SARS [29] and 2141 patients with influenza H1N1 pneumonia [30]. Finally, they did not take into consideration the updated literature reported by a Task Force Panel from the US and European critical care societies, which provided a conditional recommendation (moderate certainty) for corticosteroid treatment in ARDS [3]. What is clear from the literature is that there is a wide divergence of opinion on whether corticosteroids should be used in patients with COVID-19.

There are major differences between our study and other randomized clinical trials evaluating the impact of corticosteroids in patients with nonviral and viral ARDS. First, all the trials published before 2005 evaluated the use of steroids in patients treated with nonprotective MV [7, 8]. Second, none of the trials has used the same timing, dosage, and type of corticosteroids. Third, only one trial [8] has specifically evaluated the use of dexamethasone in ARDS. Fourth, none of the trials has consistently reassessed patients at 12 h after ARDS onset to ensure that only patients with early established ARDS were randomized. It has been shown that ARDS is characterized by an overwhelming pulmonary and systemic inflammatory response within 24–48 h resulting in exacerbated pulmonary inflammation and fibroproliferation [31]. Failure to repair tissue damage during the first 24–48 h results in an ongoing, self-perpetuating inflammation with subsequent loss of lung function and increased mortality. In our trial, we will ensure that all enrolled patients have established moderate-to-severe ARDS after 12 h of meeting the Berlin definition on standard ventilator settings.

Our study has potential limitations. First, a major limitation of our study is that it is not blinded and there is no placebo control group. However, most ICU drugs (such as dexamethasone) are administered by ICU nurses and not by physicians. Second, our study design will not allow us to conclude whether the administration of dexamethasone of different doses and for longer or shorter periods of time would have improved outcomes. Third, we powered this trial to detect a 20% risk difference, which we considered plausible in the absence of specific treatments with established efficacy in reducing mortality. We acknowledge that the minimal important difference in 60-day all-cause mortality is likely to be smaller, in the range of an absolute risk difference of 5%. However, this trial is meant as a rapid response to the COVID-19 pandemic designed to identify large signals. The conditional power analysis allows an adaptation of the sample size if the power is < 80%, but ≥ 70%, the absence of a plan to stop early for overwhelming benefit or futility means that we will maximize the information obtained while keeping the trial feasible. If the effect size is around 20% on an absolute risk difference scale, then the trial will inform clinical practice immediately, and if the effect size is smaller, it will contribute meaningfully to meta-analyses of trials addressing a similar clinical question. The major strengths of our trial are the simplicity of the study design and the use of an enrichment strategy at 12 h after initial ARDS diagnosis for assessment of moderate-to-severe ARDS under a standardized ventilatory setting.

If our hypothesis is correct, it will be the first time that treatment with a well-known anti-inflammatory drug, such as dexamethasone, will decrease morbidity and mortality of patients with established ARDS caused by COVID-19. As well, if our hypothesis is correct, expected benefits for public health will include earlier liberation from MV, less probability of complications (extubation failure, multisystem organ failure), earlier discharge from the ICU, earlier discharge from the hospital, and marked reduction of health care costs.

